# Inclusion criteria and recruitment

Infants of women intending to remain in the area for at least 2 years with a birthweight >2000 g, no acute neonatal infection and no severe congenital abnormality will be recruited. The majority of babies selected for the study will be born in hospital, but children born at home may also be included if appropriate. Note that not all mothers enrolled will have babies recruited to the study, depending on the number born in any particular week, collection of a cord blood sample and condition of the baby. Formal recruitment will begin with the routine vaccinations (BCG, OPV, HepB), which should be given within 72 hours of birth. While there will be no routine HIV testing, children of mothers known to be HIV positive will be excluded. Computer-generated lists of random numbers will be used for block randomization (see vii below).

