## Concomitant vaccine responses: Antibody responses to diphtheria toxoid (DT), tetanus toxoid (TT) and Hib at 4 months of age will be measured by standardised ELISA as previously described (81). Hepatitis B antibody will be measured using a routine clinical laboratory assay. Children having antibody levels that are not protective will be offered the appropriate booster immunization(s).

*Cellular immune responses:* Adaptive and innate immune functions will be assessed in children at birth, and at 3, 9, 10 and 18 months of age, employing methods in current usage in prospective cohort studies in Perth. The [name] laboratory has developed robust methods for immunoepidemiological field studies based upon on‑site collection of blood, and local processing to yield purified peripheral blood mononuclear cells (PBMC) which are immediately cryopreserved, and subsequently shipped under liquid nitrogen to a central laboratory for later assay. The T‑cell culture systems comprise bulk culture stimulation employing 0.5x106 cells per sample, to minimise detection problems associated with low frequency of circulating responder cells.

The choice of sampling times for T-cell studies (cord, 3, 9,10 and 18 months) is based on results from our earlier studies (64, 65) and from ongoing cohort studies. Our interest in cord blood analysis is based on recent results suggesting that neonatal cytokine production profiles are predictive of immune response capacity at age 2‑4 years (82). The sample at 3 months was chosen to provide a profile of early T‑cell immunity to Pnc antigens in unvaccinated subjects, versus those who had been given 3 vaccine doses commencing at birth or delayed until one month of age. Secondarily, it will permit assessment of possible effects of PCV on postnatal maturation of overall immune competence and/or responsiveness to index vaccine components (DT, TT). The bleeds at 9 and 10 months will permit us to assess firstly the stability of PCV carrier-specific T‑cell immunity in the different groups (6 months after the last vaccine dose), and secondly will permit assessment of the effects of PCV on the memory T‑cell response to measles, which is the third index vaccine in the study. The final bleed at 18 months will provide data on T‑cell memory to the PCV vaccine, and a logical end-point to the section of the study involving assessment of kinetics of postnatal maturation of immune functions.

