Similar to concerns with early onset Pnc carriage, neonatal immunisation with PCV may result in preferential Th2 priming for the PCV carrier protein CRM197 which may affect subsequent responses to the virtually identical DT component of DTP vaccine. The potential for non-specific interference with responses to two additional “index” vaccines, the TT component of DTP vaccine which elicits a mixed Th0‑like response in infants which includes a strong Th2 component (64, 65), and the measles vaccine which elicits a response with a stronger Th1 component, will also be assessed. T‑cell cytokine responses to all these vaccines will be measured in the three study groups, to ascertain in particular whether neonatal PCV modulates the Th1/Th2 balance in host responses. Antibody responses to concomitant TT, Hib (PRP-TT) and DT will be measured at 4 months of age to ensure that there has been no interference with humoral immune responses. In this population all children achieve protective anti-tetanus and anti-diphtheria toxin antibodies after 3 doses of ActHib (76).

*(b)* *Non-specific interference with normal maturation of the immune system, in particular Th1 immunity*

Given the important role of microbial stimulation in driving the postnatal maturation of immune function(s), it is theoretically possible that PCV, particularly if given in the neonatal period, may contribute to this drive and hence accelerate the normal maturation process. This represents a possible safety issue, as (for example) precocious postnatal maturation of Th1 function may pose potential risks for inflammatory disease. Alternatively, PCV may promote non-specific Th2 immunity and delay Th1 maturation resulting in increased susceptibility to infectious and allergic diseases. Accordingly, specific analyses will be performed to contrast the kinetics of postnatal maturation of Th1/Th2 response capacity in groups with and without neonatal PCV.

*9. The impact of PCV on respiratory morbidity in PNG infants in the first year of life*

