# **viii) Data analysis**

The principal analyses of efficacy and safety will be based on t-tests and chi-square tests. Further analyses examining the association of different factors such as number in household, housing type, town/country etc with response will use multiple regression methods: linear when IgG or cytokine level is the response, logistic when IgA, carriage or cytokine detection is the response, Cox when time to hospital admission or onset of carriage is the response, or Poisson when admission rate is the response.

Comparison of cytokine levels between the different groups at different times will employ the same basic methods; however, further analyses of immune competence will be slightly more complex in that the profile of within-person changes over time in antibody and cytokine levels will form the major response and explanatory variables. Thus 2-level models allowing for different levels of variability within and between children will be used, comparing in particular both level and rate of change of these measures. These regression models will also include terms for vaccination status as well as the other confounders such as crowding, sex etc.

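### Per-visit group comparisons of PHA- and LPS/IFN-induced cytokines name no baseline covariate although a cord-blood value of the same response is measured, which costs some precision

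*Protocol*

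**What the plan says.** Section viii) Data analysis opens with "The principal analyses of efficacy and safety will be based on t-tests and chi-square tests". Regression is reserved for further analyses of factors such as household size, housing and town or country; linear regression is named there for cytokine level. The next paragraph says "Comparison of cytokine levels between the different groups at different times will employ the same basic methods". The same sentence then turns to immune competence, where "the profile of within-person changes over time in antibody and cytokine levels will form the major response and explanatory variables", and the plan continues: "2-level models allowing for different levels of variability within and between children will be used, comparing in particular both level and rate of change". On covariates it says "These regression models will also include terms for vaccination status as well as the other confounders such as crowding, sex etc". The cord value is not named as a covariate for the per-visit comparisons, and the section does not say how the birth sample enters the 2-level models.

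Table 2 lists the PHA, LPS/IFN, PPD and SEB stimuli at birth, 3, 9, 10 and 18 months. Section v) Laboratory methods makes PHA and LPS/IFN the independent measures of Th1/Th2 maturation and runs PPD and SEB only if there are enough cells. It justifies the cord sample by recent results suggesting that "neonatal cytokine production profiles are predictive of immune response capacity at age" 2–4 years. Under Inclusion criteria and recruitment, whether a baby enters the study varies, "depending on the number born in any particular week, collection of a cord blood sample and condition of the baby". Question 8(b) in section vi) promises that "specific analyses will be performed to contrast the kinetics of postnatal maturation of Th1/Th2 response capacity in groups with and without neonatal PCV".

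**The concern.** The cord value is collected before randomisation, on the same assay as the later outcome, and the protocol itself expects cord responses to predict later immune capacity. A covariate of that kind normally belongs in the group comparison: it removes the part of the between-infant variation that was already present at birth. A plain t-test at 3, 9, 10 or 18 months leaves that variation in the error term.

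Immunological safety is a main purpose of the trial, and in a safety comparison failing to see a real shift is the costly mistake. A modest gain from samples already planned is therefore worth having. A second, smaller matter is that the 2-level models can still be touched by a chance difference at birth, depending on how the birth sample is coded.

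**Working it through.** **Inputs.** From section vii) Sample size requirements: 100 infants per group, at least 90 evaluable; 5% significance (taken as two-sided); 80% power. That section gives no SD, target difference or power for any cytokine, so differences are in SD units. The correlation r between the cord value and the later value is not in the protocol; 0.2 to 0.5 is assumed. It is also assumed that 90 per group are evaluable for cytokines.

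**Plan's nearest figure.** The protocol gives a 95% CI of 60–79% around 70%. The exact interval is 60.0–78.8% with 100 infants and 59.4–79.2% with 90, so the figure reproduces. It is used here only to fix the group size and is not disputed.

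**Step 1, the plain t-test.** The SE of a difference in means is √(2/90) = 0.149 SD. The difference detectable with 80% power is 0.149 × (1.96 + 0.84) = 0.418 SD. At 0.42 SD, power is Φ(0.42/0.149 − 1.96) = 80.4%.

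**Step 2, with the cord value as covariate.** The residual variance is 1 − r², the equivalent group size is 90/(1 − r²), and power is Φ(0.42/(0.149·√(1 − r²)) − 1.96).

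| r (assumed) | Variance removed | Equivalent n per group | Detectable difference (SD) | Power at 0.42 SD |
|---|---|---|---|---|
| 0 (t-test) | 0% | 90 | 0.418 | 80.4% |
| 0.2 | 4% | 94 | 0.409 | 82.0% |
| 0.3 | 9% | 99 | 0.398 | 84.0% |
| 0.4 | 16% | 107 | 0.383 | 86.7% |
| 0.5 | 25% | 120 | 0.362 | 90.2% |

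The proportion of variance removed depends on r alone, not on the group size or the SD.

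**Step 3, the birth sample in the 2-level models.** Assume no PCV effect, visits at 0, 3, 9, 10 and 18 months and equal correlation r between all visits. The mean visit time is 8 months, the deviations are −8, −5, 1, 2 and 10, and their squares sum to 194. The correlation between a raw slope contrast and the chance group difference at birth is then −√(1 − r) × 8/√194, which is −0.51 at r = 0.2 and −0.41 at r = 0.5. A simulation of 4,000 null trials with 90 per group gave −0.46, −0.39 and −0.31 at r = 0.3, 0.5 and 0.7; the formula gives −0.48, −0.41 and −0.31. In the same simulation the 18-month difference in means correlated with the birth difference at 0.31, 0.52 and 0.71. After adjustment for the cord value the correlation was 0.01–0.03. So a slope model does not carry a birth difference forward, but it does regress back from it unless birth is treated as baseline.

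**The case against.** The strongest objection is that nothing here is invalid. In a randomised comparison the unadjusted t-test is unbiased and holds its type I error. A reader might infer that chance imbalance at birth biases the comparison. A 0.3 SD imbalance, about two SEs (0.3/0.149), would carry 0.3 × 0.2 = 0.06 to 0.3 × 0.5 = 0.15 SD into the later difference. That is at most about one SE, and the t-test's SE already allows for it. It is a reason to adjust, not evidence of bias. This objection stands.

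A reader who stops at "Comparison of cytokine levels between the different groups at different times will employ the same basic methods" might also infer that the safety contrast on immune maturation rests on plain t-tests. It does not. The sentence goes on to within-person change, and the 2-level models of level and rate of change match the kinetics contrast of question 8(b). Questions 6(b) and 6(c) also plan to relate cord function to later maturation and colonisation, and linear regression for cytokine level is already among the further analyses. All of this stands. None of it names the cord value for the per-visit randomised comparison.

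One might further infer that including the birth visit dilutes a constant post-vaccine effect by one fifth. That needs a single group effect averaged over all five visits, a model the protocol does not specify.

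The size is open to challenge too. The source cited for prediction concerns, by its title, cord responses to SEB and PPD and the risk of atopic dermatitis; it supplies no same-stimulus correlation for PHA or LPS/IFN. The protocol's remark that maturation kinetics vary widely between infants could even point to weak tracking. Some infants may lack a usable cord result, for instance after a home birth. Finally, the coding of the birth sample could properly be settled in a statistical analysis plan that is not at hand.

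**Conclusion.** The point holds as an improvement in efficiency, not as an error. The per-visit comparisons of PHA- and LPS/IFN-induced cytokines, and of PPD and SEB where run, are planned as simple tests although a pre-vaccine value of the same response is collected. Using it would be worth the equivalent of 94 to 120 infants per group in place of 90. That size rests wholly on the assumed correlation of 0.2 to 0.5: at the lower end the gain is slight, at the upper end useful.

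The point does not extend to CRM197, DT, TT, OMP, HDM, RSV or measles responses, which Table 2 does not measure at birth. It leaves the primary outcome, serotype-specific IgG at 2 months, untouched. For the 2-level models, the only request is to say how the birth sample enters.

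**What to change.** In section viii), or in the statistical analysis plan, state three things.

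1. Groups are compared on PHA- and LPS/IFN-induced cytokines (PPD and SEB where run) at 3, 9, 10 and 18 months by linear regression on the log scale, with the infant's cord value for the same stimulus and cytokine as covariate. The t-test is kept as a sensitivity analysis.
2. In the 2-level models the birth sample is baseline, either as a covariate or as an outcome with a common mean across groups, so that a chance birth difference does not affect the level or slope contrast.
3. Infants without a usable cord result stay in the analysis, by a missing-value indicator or simple imputation chosen in advance.

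No new sample or assay is needed. The cost is the wording and the missing-value rule.

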***5. Contributions of the partners and added value of the proposed partnership***

Pneumonia is a major health priority of the PNG Health Plan. Although PNGIMR targets its research program to reflect the National Health needs, it has been difficult in recent years to obtain the funding required to maintain a strong respiratory disease program. This project, in addition to addressing a very important research question, will help PNGIMR rejuvenate its research program on respiratory diseases. PNGIMR has a long history of conducting vaccine trials and has established immunological and bacteriological facilities. This collaboration combines researchers with extensive experience in field research, epidemiology, bacteriology and immunology in PNG with state-of-the-art immunology and molecular techniques to address fundamental health issues in a high-risk population. The project will provide a critical mass of activity and training to provide a framework on which to build an ongoing program and to seek diversified funding opportunities to ensure sustainability. ICHR and the Department of Paediatrics, University of Western Australia (UDP) are members of the PNGIMR Buttressing Coalition. After 17 years as epidemiologist in PNG (where she was also training officer for PNGIMR), [name] has ongoing collaborations with PNGIMR to complete studies of ARI and the impact of vaccination on childhood mortality and is working on otitis media and respiratory bacteria in Australia. Training of PNGIMR staff in Perth in immunological techniques is ongoing with [name] and [name]. [name] is a pre-eminent cellular immunologist who has made major contributions to the understanding of immune responses to allergens and the normal maturation of the immune system. He has extended this to the generation of vaccine-specific cellular immunity in early life. [name] is a paediatric immunologist with extensive experience in vaccine trials and serological assays. [name] is the director of the IMR based in Goroka. He is a microbiologist with the field experience and ability to successfully coordinate the laboratory and field components in PNG. All collaborators will be fully involved in the study design and analysis, to which [name] will have an essential statistical input.

Invasive and mucosal Pnc infections in early infancy are a major global health burden. The potential advantages of neonatal immunization include high vaccination coverage, protection against very early Pnc carriage, reduction in mortality and morbidity due to pneumonia and IPD in early infancy, and enhancement of subsequent protection by PPV. Benefits are also likely to occur for the prevention of OM and its complications in high-risk populations. Detailed studies are essential to ensure “immunological safety” of this approach and to further our understanding of mechanisms of actions of bacterial conjugate vaccines. Public concerns over increasing numbers of vaccines overloading children’s immune system mean that in-depth immunological studies are needed globally to provide a solid basis for ensuring the safety of immunization in infants and to address these safety concerns explicitly. This study will provide basic immunological understanding to inform the epidemiological investigation of the immune responses achieved and the safety and possible non-specific benefits of immunization in a tropical setting. Furthermore, the results of this study will be particularly relevant for the prevention of Pnc disease in the ‘fourth world’ – in young indigenous children of first world countries who suffer similarly high rates of Pnc disease and early URT carriage.

Australian investigators will gain expertise in field research in non-industrialised countries, which will help enhance collaboration with groups in other countries in the region. Through detailed investigation of immune responses in infants exposed to numerous pathogens from a very young age, this collaboration will complement studies conducted in Australia towards understanding the development of the immune system in infancy.

This proposed study will have important implications for the development of pneumococcal immunization policy in PNG and other non-industrialised countries. If neonatal immunization with PCV is found to be safe, the collaborators will be in a strong position to proceed to an efficacy study and work towards establishing the most effective and cost-efficient schedules for PCV and the associated use of PPV.

